## Abstract

**Background:**

People living in care homes often have complex mental and physical health problems, disabilities and social needs which are compounded by the use of psychiatric and other drugs. In the UK dementia care is a national priority with a vast impact on services. WHELD combines the most effective elements of existing approaches to develop a comprehensive but practical intervention. This will be achieved by training care staff to provide care that is focused on an understanding of the individual and their needs; and by using additional components such as exercise, activities and social interaction to improve mental health and quality of life (QoL) and reduce the use of sedative drugs.

**Design:**

Work Package 3 (WP3) is the pilot randomised trial and qualitative evaluation to help develop a future definitive randomised controlled clinical trial. The study design is a cluster randomised 2x2x2 factorial design with two replications in 16 care homes. Each care home is randomized to receive one of the eight possible permutations of the four key interventions, with each possible combination delivered in two of the 16 homes. Each cluster includes a minimum of 12 participants (depending upon size of the care home, the number of people with dementia and the number consenting).

**Discussion:**

The overarching goal of the programme is to provide an effective, simple and practical intervention which improves the mental health of, and reduces sedative drug use in, people with dementia in care homes and which can be implemented nationally in all UK care homes as an NHS intervention.

**Trial Registration:**

Current controlled trials ISRCTN40313497

## Background

Twenty five million people worldwide have dementia, including 700,000 in the UK [1], of whom an estimated 250,000 live in care homes [1,2]. Older people with dementia in care homes have complex needs; for example, cognitive and functional impairment often coexists with additional mental health problems such as aggression, agitation, depression and psychosis [3]. These difficulties are further compounded by the widespread prescription of antipsychotic drugs [2,4]. The cost of prescription of antipsychotic medication is estimated to be £84 million a year for 140,000 people in the UK, who are unlikely to benefit and may be harmed by them [5].

Dementia has a vast impact on Health and Social Care Services. The direct cost of Alzheimer’s disease is £17 billion per year [1], greater than for stroke, heart disease and cancer combined. The high level of unmet need and the management of key health and mental health issues are matters for serious concern both nationally [6], and internationally [7]. In the UK this led to the National Dementia Strategy (NDS) [8], which was developed as a partnership between the Department of Health (DH) and key stakeholders such as the Alzheimer’s Society. It is a unique vision for people with dementia and provides a five-year plan to ‘develop services for people with dementia and their carers that are fit for the 21st century and that meet the needs of everyone’. Key goals include objective number 11 ‘Improving the quality of care for people with dementia in care homes’, achieved through a variety of measures, including visits from specialist mental health teams, and objective 13, the development of an ‘informed and effective workforce for people with dementia’, whereby health and social care staff will receive the right training and have the right skills to deliver the best care.

The National Service Framework (NSF) for older people [9], the National Institute for Clinical Excellence (NICE) dementia guidelines [10] and a market analysis [11,12] also highlight the importance of training for care staff and the need to improve access to effective non-pharmacological therapies. The DH has also conducted a review of antipsychotic prescribing [13,14] for people with dementia, which recommends a substantial reduction in unnecessary prescribing. This adds further weight to the recommendations of the NDS, the NSF and the NICE dementia guidelines to improve the treatment and care for people with dementia in care homes. Care home regulators in the US have launched initiatives to tackle the same key issues [15]. The NDS vision of enabling people with dementia in care homes to live well with dementia needs to be underpinned by effective, evidence-based interventions that are standardized, consistent, practical and can be delivered as part of the National Health Service (NHS).

Improving the care of mental health problems, reducing antipsychotic use and improving quality of life for people with dementia in care homes are all key NHS priorities. There is strong evidence that staff training, promoting person-centred care (PCC) and utilising non-pharmacological interventions improve some key health outcomes and can reduce antipsychotic drug use [10,16]. However, the breadth of benefit conferred by most of these interventions is modest; none have directly improved the quality of life (QoL) for care home residents with dementia, and importantly, none have achieved widespread implementation in a health or care setting as part of routine NHS practice.

Further research is therefore urgently needed to address these key issues. There is a need for an optimised therapy combining the most effective elements of currently available evidence-based interventions that are conceptually integrated, cost-effective and practical to implement in a range of settings. To achieve these objectives there is a need to evaluate the key components of effective interventions to enable the development of an optimised intervention.

Overcoming the barriers to implementation, which is rare in dementia care research and has never been achieved for any therapy in a care home setting, is also a major challenge. Research is needed to tailor an optimised therapy to the needs of mental health practitioners, care home staff and people with dementia in care homes. In addition, research should identify and overcome the potential obstacles to implementation, and refine the intervention model through in-depth field testing. This programme aims to provide an effective, simple and practical intervention that improves mental health and reduces sedative drug use for people with dementia in care homes, and which is replicable and scalable to enable it to be widely used in the UK and internationally. The current paper describes the pilot study and qualitative evaluation, setting the foundation for the full-scale multicentre randomised controlled clinical trial to evaluate an optimised intervention ‘welding together’ the most effective elements of the best currently available intervention programmes and a standardised manual and training programme (WHELD).

### Study objectives

The pilot study follows a factorial randomised controlled clinical trial design. Evaluations will be undertaken to understand the breadth of additional benefits conferred by three interventions, namely, antipsychotic review (discontinuation and safety); social interaction and pleasant activities; and exercise, compared with PCC alone.

### Hypotheses

Each intervention will significantly improve several key outcomes but none when used alone will improve all outcomes. This pilot randomised trial is not powered to provide a definitive answer but to guide the analysis and to generate firm hypotheses for testing in a definitive large-scale cluster randomised trial.

Specifically the hypotheses are that compared to person-centred care alone are:

1. PCC plus antipsychotic review will result in the reduction of antipsychotic prescribing.

2. PCC and social interaction with pleasant activities will result in reductions in agitation/aggression, especially in individuals already experiencing these symptoms at the baseline evaluation.

3. PCC and exercise will improve mood and reduce falls.

### Secondary objectives and qualitative evaluation

To inform subsequent work, the key secondary objectives are to determine the specific impact of each therapy on a range of outcomes including, mental health, psychotropic drug use, physical health and QoL, as well as the impact on potentially important mediating factors such as activities, social interaction, staff attitudes and the quality of the interaction between care staff and people with dementia.

The purpose of the qualitative research is to develop understanding of the process of implementation within the care environment. Staff beliefs, attitudes and behaviour in their work with people with dementia are key components. Recognition and acknowledgement of staff perspectives is also essential to negotiating the implementation of the interventions.

## Methods/Design

### Overall design

The study design is a cluster-randomised, 2 × 2 × 2 factorial design (with two replications), pilot study in 16 care homes, as shown in Figure 1. Each cluster includes a minimum of 12 participants (depending upon the size of the care home, the number of people with dementia and the number consenting). Each cluster receives a randomly allocated intervention for a minimum of nine months. Evaluations will be undertaken to understand the breadth of benefits conferred by three key interventions to be assessed when used in addition to the person-centred care training package, where efficacy has already been established. The flow chart for the research is shown in Figure 2.

**Figure 1 F1:**
[figure not shown]
Design and consort diagram.

**Figure 2 F2:**
[figure not shown]
Flow chart for work plan 3.

The WHELD PCC intervention primarily uses the tools developed in evidence-based approaches for improving care in care homes in the operationalized *Focussed Intervention, Training and Support* (FITS) manual [17], which has demonstrated efficacy in a robust randomised controlled trial (RCT) [18]. Additional supplementary materials have been drawn from the best available training manuals from a robust review of available materials conducted as part of the WHELD study, and augmented by elements of leadership training on the basis of input from an expert therapy development group. The intervention has 5 focii:

1. Embedding an understanding of dementia and PCC.

2. Assessing how home practices deliver PCC.

3. Understanding the relationship between an individuals’ experience and individuals’ behaviour and well being.

4. Recognising the impact of staff-resident interactions on the care experience.

5. Implementing PCC planning based on these principles.

This training package will be delivered to all staff in the participating care homes.

Antipsychotic review will involve specific review of antipsychotic drugs by participants’ own General Practitioners (GPs) or psychiatry specialists, based upon the principles outlined in the NICE dementia guidelines, and facilitated by an antipsychotic care pathway developed by the Alzheimer’s Society in partnership with the DH [13]. GPs will be offered an initial seminar outlining the best practice guidelines, and prompted when 12-week antipsychotic reviews are due according to NICE/Social Care Institute for Excellence (SCIE) guidelines. Care home staff will be offered a seminar on safe prescribing, monitoring and review of antipsychotic drugs. In addition, for all participants continuing to receive antipsychotic drugs after the initial review, or where antipsychotic drugs are started or re-started, a detailed medical antipsychotic care plan will be advised, using the principles outlined in the antipsychotic care pathway. This will include planned dates for further antipsychotic review.

For social interaction with pleasant activities, an intervention manual will be developed based upon three evidence-based approaches and specific communication skills training to enhance staff-resident interactions: (1) the positive events schedule, shown to be effective in the treatment of agitation and depression in people with dementia in non-care home settings [19,20]; (2) the social interaction intervention developed by Cohen-Mansfield and colleagues [21], which is useful for reducing agitation in people with dementia in care homes; and (3) the Needs, Environment, Stimulation, and Technique (NEST) programme, developed by Buettner and colleagues [22], which has been shown to be effective in improving cognitive function and reducing agitation and depression. Minor adaptations will be undertaken, in collaboration with the authors who developed the manuals, to ensure that they are suitable and practical for administration in UK care homes.

For exercise, the main focus will be to promote exercise through encouraging enjoyable positive physical activities. Teri and colleagues have developed an effective approach, based on their positive event schedule but focused on exercise-based activities [20]. The NEST manual [22] and the Range of Motion (ROM) dance programme [23], which an RCT has shown to be effective for older people with arthritis in care settings [24], will be used as specific resources to offer people enjoyable individual and group exercise activities to augment activities identified as hobbies or enjoyable activities by individual participants.

The factorial design is shown below. For example, care homes 1 and 9 will receive PCC only, while care home 4 will receive social interaction and exercise in addition to PCC and care home 13 will only receive antipsychotic review in addition to PCC. Staff will receive training in the interventions allocated to the care home, with all care homes receiving training in the PCC intervention.

Each intervention is delivered by two trained therapists, who have received an intensive 10-day training package and who will coordinate the delivery of the intervention into eight care homes. In each care home two lead members of the care staff (WHELD champions) will be trained to implement the intervention.

### Number of participants and power of the study

Sixteen suitable care homes to be identified, recruited and randomised, with the intervention delivered to all residents, with a minimum recruitment target of 12 individuals with dementia per care home. All residents within the care homes, who meet the study’s eligibility criteria will be invited to participate, which will help to account for the potential loss of participants during the course of the study. Baseline and follow up data will be collected on all consenting residents who meet the inclusion criteria at each participating care home. This is an exploratory pilot study whose main purpose is to collect data to enable the design and sample size calculation for the definitive RCT. As such, the size of effect for the outcome measures, their SDs and intra-class correlations (ICCs) are unknown.

### Randomisation

A restricted randomisation method will allocate the eight interventions to the eight care homes in the two samples. The randomisation will be performed as a constrained complete list randomisation, meaning that all care homes will have been recruited before the randomisation is performed. The constraint ensures an approximately equal distribution of the number of interventions to each geographic location. The randomisation system used has been coded and validated in R (statistical package). The R Foundation for Statistical Computing c/o Institute for Statistics and Mathematics, Vienna, Austria.

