### Quantitative data analysis

With the exception of the quality of interaction schedule (QUIS) observational study, which is conducted at a group level, all outcome data will be collected at an individual level for the individual participants. Outcome measures for pilot evaluation will be assessed at baseline and nine months and are listed in Table 1. All the outcome measures collected will be described and reported using appropriate descriptive statistics, tabular and graphical techniques. Particular note will be taken of baseline SDs and overall effect sizes. These data will be used to inform power calculations for Work Plan 5 (WP5). The change from baseline in the PCC group will quantified and fully described.

The CONSORT diagram information will be assessed to identify potential differences in dropout rates and other data quality issues in order to inform the design of WP5. A more detailed statistical analysis plan will be drawn up prior to analysing the data, which will be approved by the programme steering group and the Data Monitoring and Ethics committee.

The analysis of outcomes will involve a multilevel analysis of variance (ANOVA) model for the 2 × 2 × 2 factorial design with two replications among the care homes and participants, clustered within each care home. The three factors being examined are the presence or not of antipsychotic review, of social interaction and of exercise. The two replications refer to the two lists of care homes, those previously known and those not known to the investigators. Means with 95% confidence intervals will be quoted and a 5% significance level will be reported. As this is a hypotheses-generating pilot study, no adjustment will be made for multiple comparisons.

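### The randomisation constraint, as worded, equalises a count of interventions per location and does not assure that each of the three factors is balanced within location

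*Protocol article*

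**What the plan says.** Under Randomisation, the protocol article says that "A restricted randomisation method will allocate the eight interventions to the eight care homes in the two samples", so each of the eight factorial combinations is used once in each sample of eight homes. It is a complete-list procedure: "all care homes will have been recruited before the randomisation is performed", which means that every home's location is known when the allocation is drawn. The restriction is then given in one sentence: "The constraint ensures an approximately equal distribution of the number of interventions to each geographic location".

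The word intervention has no fixed meaning in the article. In the Randomisation section it denotes the eight combinations. Under Study objectives and Overall design it denotes the three components added to person-centred care. The Abstract counts four.

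Under Quantitative data analysis the comparison is by component: "The three factors being examined are the presence or not of antipsychotic review, of social interaction and of exercise". The model is a multilevel ANOVA with these factors, the replications and clustering by home. Replication is not a stand-in for area: "The two replications refer to the two lists of care homes, those previously known and those not known to the investigators". Location is not named. The same section announces a more detailed SAP, to be written before the data are analysed.

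**The concern.** The restriction should protect the comparisons that will be made, which are three on-versus-off contrasts with eight homes on each side. A rule about the number of interventions per location protects them only if it is read in a particular way.

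- If interventions are the eight combinations, each home has exactly one. Their number in a location is then the number of homes there, and no factor is constrained.
- If the number is the count of added components, the totals are equalised, but one factor can be over-represented in a location while another is under-represented.
- If the sentence means that each component is spread evenly over locations, it does the job, but it does not say so.

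Area can plausibly matter. Antipsychotic use is a primary outcome in Table 1, and the review is carried out by residents' own GPs or psychiatry specialists, so local prescribing practice bears on it. The investigators themselves thought location worth restricting on. With 16 homes, chance imbalance does not average out. The pilot's effect sizes and SDs are meant to inform the sample size of the definitive trial, so a contrast that carries part of an area difference would be passed on.

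**Working it through.** The article gives no balance figure to reproduce. The design count checks: 8 combinations × 2 replications = 16 homes, with 8 on and 8 off for each factor, and at least 16 × 12 = 192 residents.

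**Assumptions.** The number and size of locations are not stated. I take two equal locations, with 4 + 4 homes in each replication. ICCs are declared unknown in the article, so those below are assumed as well.

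**Step 1: one replication, equal component totals.** The eight combinations carry 12 components in all.

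- Possible splits into 4 + 4: C(8,4) = 70.
- Splits with 6 components in each location: 20.
- Of these 20, 8 have every factor at 2:2. The other 12 have one factor at 3:1, one at 1:3 and one at 2:2. For example, the homes 000, 001, 011 and 111 together in one location give factor counts 1, 2 and 3, with a total of 6.
- A given factor is 2:2 in 12 of 20 (0.6), 3:1 in 4 of 20 (0.2) and 1:3 in 4 of 20 (0.2).

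**Step 2: both replications, with the rule applied in each.** For a given factor over 16 homes:

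- 4:4 has probability 0.6² + 2 × 0.2 × 0.2 = 0.44.
- 5:3 in either direction has probability 2 × 0.6 × 0.4 = 0.48.
- 6:2 in either direction has probability 2 × 0.2² = 0.08.

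Taking the worst of the three factors over the 20 × 20 = 400 allocations: all are 4:4 in 88 (22%), the worst is 5:3 in 240 (60%), and the worst is 6:2 in 72 (18%).

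**Step 3: what enters the contrast.** With a homes on in location A and 8 − a on in location B, the off homes number 8 − a in A. The share of a location difference that enters the unadjusted contrast is [a − (8 − a)]/8.

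- 5:3 gives (5 − 3)/8 = 0.25.
- 6:2 gives (6 − 2)/8 = 0.50.

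**Step 4: the combination-count reading.** All 70 splits are then allowed. A given factor has 0, 1, 2, 3 or 4 on-homes in location A in 1, 16, 36, 16 and 1 of the 70. Over 70² = 4,900 allocations it is 4:4 in 1,810 (37%), 5:3 in 2,368 (48%), and 6:2 or worse in 722 (15%).

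**Step 5: can factor balance be reached?** With 4 + 4 homes, yes: 8 of the 70 splits per replication have every factor at 2:2. With 3 + 5, exact balance is impossible, and the smallest worst-factor difference in share is 0.27.

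**Step 6: precision if location is balanced but not modelled.** With 12 residents per home, the variance of a home mean in units of total variance is v = ICC + (1 − ICC)/12. If location explains a fraction f of the between-home variance, leaving it out widens the interval by √[v/(v − f × ICC)].

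- ICC 0.05, f = 0.3: √(0.1292/0.1142) = 1.06.
- ICC 0.10, f = 0.5: √(0.175/0.125) = 1.18.

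**Step 7: the price in degrees of freedom (97.5% t quantile).**

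| Model | Without location | One df for location | Two df | Three df |
|---|---|---|---|---|
| Main effects + replication | 11 df, 2.201 | 2.228 (+1.2%) | 2.262 (+2.8%) | 2.306 (+4.8%) |
| Full factorial + replication | 7 df, 2.365 | 2.447 (+3.5%) | 2.571 (+8.7%) | 2.776 (+17.4%) |

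With the full factorial, the low-end gain of 1.06 falls to 1.06/1.035 ≈ 1.03 with two locations and becomes a loss with three (1.06/1.087 ≈ 0.98). With four locations the high-end gain of 1.18 is almost gone (1.183/1.174 ≈ 1.01).

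**The case against.** The strongest reply is that the sentence is ambiguous, not wrong. Study objectives and Overall design use the word for the three components. On that usage, an even spread of interventions over locations could be close to the factor-by-factor rule asked for here. The randomisation program is described as coded and validated, and it is not shown. The combination-count reading makes the restriction empty, which is a reason to doubt that it was meant. All this stands, and it is why the point is put as what the wording fails to assure and not as a fault in the program.

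Second, further model terms are commonly left to the SAP, and the article announces one. That stands too: the omission is established only for the model outlined in the article.

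Third, this is a hypothesis-generating pilot, and between-home degrees of freedom are scarce. That limits the stakes and makes the location term a matter of judgement when areas are many.

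A reader might infer that a component could be wholly confounded with location. Under equal component totals with two equal locations it cannot be: placing all four homes with a given factor in one location would give 8 components there and 4 in the other. Nor is any component steered to an area, since the allocation is random and follows recruitment; an imbalance can fall either way. A reader might also infer that the restriction is wasted if location is not modelled. It is not: balance that is achieved protects the unadjusted contrasts. What is lost is precision and the correction of any imbalance that remains.

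**Conclusion.** The concern holds in a limited form. The constraint as written does not assure balance of each analysed factor within location, and the outlined model has no term that would correct what imbalance remains. Under the assumed two equal locations and equal component totals in each replication, a given factor is unbalanced in 56% of allocations, mostly mildly (48% at 5:3, 8% at 6:2), with a quarter or a half of any location difference entering its unadjusted contrast. These percentages depend on the assumed number and size of locations. The 6% to 18% excess width of intervals that omit a balanced location depends on an assumed ICC and location share of variance, and is before the loss of degrees of freedom. The documents support neither complete confounding nor the statement that the final analysis will ignore location. The consequence is limited to the estimates that the pilot hands to the definitive trial.

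**What to change.** Reword the constraint under Randomisation along these lines: *within each replication, each of the three factors is present in as near as possible half of the homes in each geographic location*, with the allocation drawn at random from all those that satisfy it. State how many locations there are. If the program already does this, the sentence alone needs correcting. If homes have already been allocated, report the factor-by-location table.

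In the model under Quantitative data analysis, or in the SAP, include location as a fixed effect, merging areas with few homes so that it uses only one or two between-home degrees of freedom; otherwise say why it is left out.

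The cost is a few lines of R and one model term. The set of admissible allocations shrinks (8 in place of 20 splits per replication under the assumed layout), and exact balance may not be reachable with unequal locations. The t multiplier rises by about 1% to 3% with main effects only, or 3% to 9% with the full factorial, against the assumed gross gain in precision. That gain can vanish if many locations are fitted, hence the merging.
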